#### Laboratory variables analysis

Biological parameters will be summarized by group of treatment and overall at each time of measurement.

All abnormal variables will be graded and each parameter will be counted by grade.

The number of patients with abnormal data will be compared by grade between each treatment group and over the 2 years of follow-up

Transition tables will be provided between D0, D7 and D28 in order to assess the evolution of these parameters classified as normal/abnormal and by grade according to the laboratory ranges.

Absolute and relative changes to the baseline will be computed for each parameter for each attack. The evolution between D0 and D7 and D0 and D28 will be analyzed for each attack

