- Molecular biology methods (PCR): Each time a thick blood smear is obtained blood will also be collected onto filter paper. Samples will be collected by venipuncture or by fingerprick sampling. Blood will be placed onto filter paper in approximately 25 ul aliquots per blood spot. The samples will be labelled, air-dried and stored in small, sealed sample bags at ambient temperature with desiccant. Parasite DNA will subsequently be removed from the filter paper and prepared for molecular analysis using a chelex extraction method. Genotyping will be performed on all patients with outcomes classified as LCF or LPF. Genotyping of parasites collected at baseline (day 0) and the day of recurrent parasitemia will be done to distinguish between true recrudescence and new infections.

Molecular studies will be performed only for research purposes and will have no impact on the clinical management of study patients.

- Anaemia will be assessed by the haemoglobin levels on D0, D3, D7, D14, D28 and D42 if there is still an abnormal value on D28. Haemoglobin measurements shall be done by haemacue or a haematology coulter.

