### Biological tolerability

- Haematology and biochemistry will be routinely performed on days 0, 7, and 28. Haematology and biochemistry will be repeated on Day 14 and 42 if results are abnormal on Day 7 and Day 28 respectively. Haematology and biochemistry may be performed on any other day if the clinician feels results are necessary for patient management. An additional haemoglobin evaluation will be performed on day 3 from blood collected by a fingerprick and read using a portable spectrophotometer (Haemacue). Blood samples for haematology and biochemistry will be collected from patients by venipuncture. About 2 mls of blood will be drawn from each patient for biochemistry/haematology during these visits. Additional venipunctures will be performed, as appropriate, for follow-up of adverse events.

Laboratory analyses are described in Appendix 6

- Haematological parameters: haemoglobin, platelets, leukocytes, neutrophils.These parameters will be measured by a complete blood count and assay of haemoglobin and measurements shall be done by a haematology coulter
- Biochemical parameters: blood creatinine, total bilirubin, ALT. These parameters will be measured according to the enzyme assay methods for each parameter.

Note: Any abnormal laboratory (at least grade 3) value will be immediately rechecked, in case of confirmation all investigations to know the reason will be performed and the patient will be followed until normalization. The possible withdrawal of the patient from the cohort will be taken by the investigator.

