### Post-treatment follow-up visits on D7 (+/-1), D14 (+/-1), D21 (+/- 1), D28 (+/- 2) and end-of-study visit on D42 (+/- 2)

- Physical examination
- Axillary temperature
- Clinical safety
- Haematological and biochemical analyses on D7 and D14 (if abnormal results are obtained on D7, except for Hg systematically dosed on D14) on D28 and D42 (if abnormal results are obtained on D28);
- Filter paper blood spot sample for eventual DSAQ or L dosage on D7 only
- Thick and thin smear (and filter paper blood spot samples for eventual PCR)
- Concomitant treatments
- Adverse events

In the event of a positive thick film, a PCR analysis will be carried out on the corresponding blood spot sample.

If a patient cannot perform one visit all efforts will be made to review him/her at the next visit.

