#### Analysis of secondary efficacy variables

Non inferiority analysis will be performed on the same way than for the main criterion for

- before PCR corrected cure rate at D28 for the first attack
- before and after PCR corrected cure rate at D28 for the following attacks
- before and after PCR corrected cure rate at D42 for all attacks

An analysis for repeated measurements will be performed. A model will be built in order to explain the success/failure of the response. The rank of the attack, the group of treatment and their interaction will be included in the model. Some other relevant parameters could be included if descriptive analysis find out discriminating items.

Comparison between treatment groups will be provided for the following parameters

- Time to parasitological clearance for the 1st episode (number of patients without parasite from D1 to D3)
- Time to fever clearance for the 1st episode (number of patients without temperature from D1 to D3)
- Proportion of patients without fever at D3 for repeated attacks
- Proportion of patients without parasite at D3 for repeated attacks
- Evolution of number of gametocyte carriers and mean values of gametocyte rate during the 42 days of follow-up for each episode
- Evolution of hemoglobin value for each patient during each attack (between D0 and D28) occurring during the 2 years of follow up
- Evolution of mean hemoglobin values at D0,D3, D7,D14 and D28 of each episode during the 2 years of follow up
- Evolution of Hackett score during the 2 years of follow up

The number of malaria attacks will be summarized by treatment group and overall.

The evolution of average duration between 2 attacks during the 2 years of follow up will be computed and analyzed using survival analysis methods.

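### Laboratory summaries at D14 and D42 describe mainly children retested for an earlier abnormality, and the protocol schedules D14 haemoglobin in two incompatible ways

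*Protocol*

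**What the plan says.** Protocol section 10.2.2 sets the sampling: "Haematology and biochemistry will be routinely performed on days 0, 7, and 28", and "Haematology and biochemistry will be repeated on Day 14 and 42 if results are abnormal on Day 7 and Day 28 respectively". It also allows tests on other days when the clinician needs them. Section 13.2.4 and the flow-chart footnotes in section 2.1 follow the same conditional scheme.

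Section 14.5.4.2 then states: "Biological parameters will be summarized by group of treatment and overall at each time of measurement". D14 and D42 are times of measurement, and nothing in that sentence separates them from the routine visits. In the same section the transition tables use D0, D7 and D28, and the analysed changes are D0 to D7 and D0 to D28.

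Haemoglobin is treated differently in different places. Section 10.2.2 includes it in the conditional group ("Haematological parameters: haemoglobin, platelets, leukocytes, neutrophils") and makes no exception for D14. Section 13.2.4 makes D14 analyses conditional with one exception: "if abnormal results are obtained on D7, except for Hg systematically dosed on D14" (Hg is this protocol's shorthand for haemoglobin). Section 10.1.3 says: "Anaemia will be assessed by the haemoglobin levels on D0, D3, D7, D14, D28 and D42 if there is still an abnormal value on D28", where the condition attaches to D42. Sections 14.3.2.2 and 14.5.3.2 list as a secondary efficacy comparison: "Evolution of mean hemoglobin values at D0,D3, D7,D14 and D28 of each episode during the 2 years of follow up".

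**The concern.** A by-visit table is normally read as the course of one group over time. Here D0, D7 and D28 describe all attending children, while D14 and D42 describe mostly those who had just given an abnormal result. A reader following ALT or neutrophils across the columns could take the change of denominator for late toxicity or slow recovery.

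The by-arm columns raise a second problem. The retested group is formed by a result obtained after randomisation, which treatment itself may influence. Randomisation therefore does not protect an arm contrast at D14 or D42.

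The haemoglobin conflict concerns data collection. If the site follows section 10.2.2, children normal at D7 have no D14 value. One point of a planned efficacy curve then rests on a selected subset, and no later analysis plan can recover the missing values.

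**Working it through.** The protocol gives no figure on this point, so there is none to reproduce. The check compares the schedule with the analysis text and then illustrates the size under stated assumptions.

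**Schedule against analysis**

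| Measurement | D0, D7, D28 | D14 | D42 |
|---|---|---|---|
| Platelets, leukocytes, neutrophils, creatinine, bilirubin, ALT | all | if D7 abnormal | if D28 abnormal |
| Haemoglobin, section 10.2.2 | all | if D7 abnormal | if D28 abnormal |
| Haemoglobin, sections 10.1.3 and 13.2.4 | all | all | if D28 abnormal |
| By-visit summary, section 14.5.4.2 | yes | yes | yes |
| Transition tables and analysed changes | yes | no | no |

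Haemoglobin is also taken in everyone at D3. In the text available the flow chart cannot settle the D14 conflict, because the symbol linking the D7 footnote to its rows was lost in extraction.

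**Assumptions for size.** Standardised values at the two visits are bivariate normal, with the same true abnormal rate p at both and within-child correlation ρ from 0.3 to 0.9. None of these comes from the protocol. The 200 children per arm do (section 8.1).

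**Trigger read per parameter.** The rate among those retested is π₁ = P(abnormal at both visits) / p. The mean shift towards abnormal is ρ·φ(z_p)/p, where φ(z_p)/p is 2.063, 1.755, 1.400 and 0.966 for p of 5%, 10%, 20% and 40%.

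**Trigger read as any of seven parameters, taken as independent.** The share retested is S = 1 − (1 − p)⁷. With π₀ = p(1 − π₁)/(1 − p), the abnormal rate among those retested is [p·π₁ + (S − p)·π₀]/S, and the mean shift is ρ(1 − p)⁶φ(z_p)/S.

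Example: p = 0.10, ρ = 0.9, π₁ = 0.689. Then S = 1 − 0.9⁷ = 0.522, π₀ = 0.1 × 0.311/0.9 = 0.0346, and the rate is (0.0689 + 0.422 × 0.0346)/0.522 = 0.160. A simulation of 200,000 children also gave 0.160.

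| True abnormal rate | Per parameter: retested of 200 | Abnormal among retested | Mean shift, SD | Panel: retested | Abnormal among retested | Mean shift, SD |
|---|---|---|---|---|---|---|
| 5% | 10 | 14.3–63.7% | 0.62–1.86 | 30% | 6–12% | 0.08–0.23 |
| 10% | 20 | 21.6–68.9% | 0.53–1.58 | 52% | 11–16% | 0.05–0.16 |
| 20% | 40 | 33.1–75.0% | 0.42–1.26 | 79% | 21–24% | 0.03–0.08 |
| 40% | 80 | 51.5–82.6% | 0.29–0.87 | 97% | 40–41% | 0.01–0.02 |

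Ranges run from ρ = 0.3 to ρ = 0.9. At ρ = 0 there is no distortion.

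**Haemoglobin, if D14 were sampled only after an abnormal D7 value.** With an assumed SD of 1.5 g/dL, ρ of 0.4 to 0.8 and the per-parameter formula:
- 5% to 20% abnormal: from 1.400 × 0.4 × 1.5 = 0.84 to 2.063 × 0.8 × 1.5 = 2.5 g/dL lower.
- 50% abnormal (φ/p = 0.798): 0.5 to 1.0 g/dL lower.
- 80% abnormal (φ/p = 0.350): 0.2 to 0.4 g/dL lower.

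**The case against.** The strongest reply is that section 14.5.4.2 already confines its transition tables and change analyses to the systematic visits. What remains is one descriptive sentence, and labelling conditional rows or showing numbers tested is ordinary work for an analysis plan. No formal arm test at D14 or D42 is specified for the conditional parameters. The arm comparison that is specified counts patients by grade, and leaving normal children untested does not inflate a count. No tested-only denominator is stated for percentages either. On haemoglobin, the specific exception in 13.2.4 can be read as overriding the general sentence in 10.2.2, which leaves the D14 mean unselected.

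Much of this stands and limits the point. It does not remove it. The summary at every measurement time is a stated rule, and section 14.1 makes section 14 the basis of the analysis plan. Means at D14 and D42 can only come from children tested, whatever denominator is chosen for percentages, and the rule sets them out by arm. An override between two haemoglobin instructions is an inference the site should not have to make.

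A reader might go further and infer that D14 and D42 will show false toxicity, or that the D14 haemoglobin mean will dip by 0.8 to 2.5 g/dL. The documents do not support either as a prediction. The wording of 10.2.2 can naturally be read as repeating the whole panel, under which the distortion may be negligible. The haemoglobin range also requires the site to disregard 13.2.4 and only 5% to 20% of children to be abnormal. Appendix 3 grades haemoglobin as abnormal below 10 or 11 g/dL depending on age, and section 8.2.2 admits children down to 5 g/dL, so a much higher share is plausible.

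**Conclusion.** The point holds in a limited form. Followed as written, section 14.5.4.2 yields D14 and D42 means, and percentages if taken among those tested, that are shifted towards abnormal by selection and cannot be compared between arms. The direction needs only a positive within-child correlation. The size runs from negligible (40% to 41% against an assumed 40%) to more than twelvefold (64% against an assumed 5%), depending on an undefined trigger and on rates and correlations that the protocol does not give.

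Transition tables, D0–D7 and D0–D28 changes, and counts of patients by grade are not affected in this way. Nor is the primary endpoint.

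The D14 haemoglobin contradiction is a separate defect that needs no assumption. It matters because the D14 mean is a planned secondary comparison and uncollected values cannot be restored.

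**What to change.** 1. In section 14.5.4.2, limit by-visit laboratory summaries and any arm comparison to the systematic visits: D0, D7 and D28, plus D3 and D14 for haemoglobin once its schedule is reconciled.
2. Report conditional D14 and D42 results as paired follow-up of the children abnormal at D7 or D28 (resolved, persisting, worse), with the number tested in each arm. List tests ordered at clinician discretion separately.
3. State whether the abnormality trigger is read per parameter or per panel, so that the retested group can be identified.
4. Reconcile sections 10.1.3, 10.2.2 and 13.2.4 on D14 haemoglobin, so that collection supports the planned D0–D3–D7–D14–D28 analysis.

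The cost is one reconciling clause and some analysis wording. No tests are needed beyond those section 13.2.4 already lists. Item 4 needs to be settled before sampling; the others can be settled before database lock.

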### Inclusion criteria for each attack (except the failures)

- Body weight ≥ 5 kg
- Able to be treated by oral route
- Fever (axillary temperature ≥ 37.5 degrees Celsius) at D0 or history of fever within the previous 24 hours (this criteria is not required in case of late failure after D14 in the previous attack)
- confirmed *Plasmodium falciparum* infection with positive parasitemia
- Haemoglobin value ≥ 5.0 g/dl;
- Agreement to comply with the study protocol

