### Impact of repeated treatment on clinical and biological tolerability

All adverse events will be catalogued based on their frequency, severity, and relationship to study medication using standardized protocols (Appendix 2). These indices of safety and tolerability among treatment groups will be compared using each episode of malaria treated with a study drug as the unit of analysis. The same analyse will be done with the biological parameters.

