## Analysis variables

### Demographic and baseline characteristics

The demographic data and parameters recorded on inclusion will undergo a descriptive analysis according to treatment groups on the safety population.

The evaluations used as baseline values will be the last evaluations performed before treatment administration. Any repeated evaluations will be considered baseline values if performed prior to the first intake of treatment.

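### The two-year count of patients with abnormal laboratory data is neither limited to new or worsened post-dose grades nor scaled to treated attacks, and its unit conflicts with section 10.2.3

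*Protocol*

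**What the plan says.** Section 14.5.4.2 (Laboratory variables analysis) first provides that "All abnormal variables will be graded and each parameter will be counted by grade" and then states the between-arm comparison: "The number of patients with abnormal data will be compared by grade between each treatment group and over the 2 years of follow-up". Neither sentence gives a time window relative to dosing, a condition of worsening, or a per-attack denominator. The same section adds "Transition tables will be provided between D0, D7 and D28", and absolute and relative changes from baseline for each attack.

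Section 10.2.2 (Biological tolerability) sets the sampling: "Haematology and biochemistry will be routinely performed on days 0, 7, and 28". It adds "Haematology and biochemistry will be repeated on Day 14 and 42 if results are abnormal on Day 7 and Day 28 respectively", and haemoglobin is also measured on D3. Section 13.2.4 adds a systematic haemoglobin on D14. Section 14.3.1 defines baseline: "The evaluations used as baseline values will be the last evaluations performed before treatment administration". D0 is therefore the pre-dose value.

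Section 10.2.3, on the impact of repeated treatment, says that safety indices will be compared between arms "using each episode of malaria treated with a study drug as the unit of analysis" and that biological parameters will be handled in the same way.

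Section 14.5.4.1, by contrast, restricts treatment-emergent adverse events to those that began or got worse after the first dose, attack by attack.

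**The concern.** Comparing the drugs on biological tolerability is a stated objective for the first attack, for repeat attacks and for the whole follow-up (section 6.2). The comparison fixed for it has three weaknesses.

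- **Pre-dose values are not excluded.** A D0 sample is taken in a febrile child with malaria before any study drug for that attack. Graded abnormality there is possible by design: the per-attack entry criterion is "Haemoglobin value ≥ 5.0 g/dl", while Appendix 3 already grades haemoglobin below 7.0 g/dL as grade 3. Counted in both arms, such values dilute a real drug difference.
- **Exposure is not equalised.** Routine blood is scheduled only within attacks, so a child with more attacks has more chances to be counted. The number of attacks is itself compared between arms (sections 10.1.2 and 14.3.2.2). If it differs, the patient count differs even when each course is equally safe.
- **The unit is contradictory.** Section 14.5.4.2 counts patients over two years; section 10.2.3 counts treated episodes. The two give different numerators, denominators and tests for the same parameters.

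The practical risks are a missed laboratory signal, or an apparent signal that comes only from attack frequency.

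**Working it through.** The protocol gives no figure for this comparison, so there is nothing to reproduce. The calculations show the size of each effect under stated assumptions.

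**Inputs from the protocol:** 200 per arm (section 8.1); two-sided 5% chi-square or Fisher test (section 14.5).

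**Assumed, because the protocol gives no values:** D0 prevalence of abnormality, risk of a new post-dose abnormality, attacks per child, and variation between children in attack rate.

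**Test.** For true proportions p1 and p2 with mean p̄ and difference d, the rejection probability is Φ((d − 1.96·s0)/s1) plus the small opposite tail, where s0 = √(2p̄(1 − p̄)/200) and s1 = √([p1(1 − p1) + p2(1 − p2)]/200).

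**1. Dilution at the first attack.** Let the new post-dose abnormality risk r be 5% v 15%, and let q0 be the D0 prevalence, equal in both arms and independent of r. If D0 values count, the probability of being counted is 1 − (1 − q0)(1 − r), so the 10-point difference shrinks to (1 − q0) × 10 points.

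| q0 | Counted, arm 1 v arm 2 | Difference | Power |
|---|---|---|---|
| D0 not counted | 5.0% v 15.0% | 10 points | 92% (92-93% by simulation) |
| 30% | 33.5% v 40.5% | 7 points | 30% |
| 50% | 52.5% v 57.5% | 5 points | 17% |
| 70% | 71.5% v 74.5% | 3 points | 10% |

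**2. Dilution over two years.** Let attacks per child be 1 + Poisson(m − 1), so that the probability of ever being counted is 1 − (1 − q)·exp(−(m − 1)q), with per-attack q = 1 − (1 − q0)(1 − r). With m = 5 in both arms and r = 2% v 5%, power is 94% if D0 values do not count. It falls to 52%, 30%, 14% and 6.5% at D0 prevalences of 5%, 10%, 20% and 40% per attack. Over many attacks, even a modest D0 prevalence matters.

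**3. Unequal attack numbers, no drug effect.** Use the same per-attack risk p in both arms, and attacks = 1 + Poisson((m − 1) × gamma frailty) with frailty variance v = 0.3. The probability of ever being abnormal is then 1 − (1 − p)(1 + v(m − 1)p)^(−1/v).

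| p per attack | Ever abnormal, 8 v 10 attacks | Rejection, 8 v 10 | Rejection, 6 v 8 | Rejection, 8 v 8 |
|---|---|---|---|---|
| 2% | 14.6% v 17.8% | 14% | 17% | 5% |
| 5% | 31.9% v 37.7% | 23% | 30% | 5% |
| 10% | 52.3% v 59.4% | 30% | 42% | 5% |

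Without frailty the rates at 8 v 10 are 15%, 26% and 38%. At 4 v 5 attacks they run from 10% to 38% for p between 2% and 40%. A per-attack risk is equal in both arms by construction here, so a per-attack comparison that allows for clustering keeps its 5% level whatever the attack counts.

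**The case against.** Four counter-arguments have weight.

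- **Other laboratory comparisons exist.** A reader might infer that this count is the only between-arm laboratory analysis, or that a drug effect on anaemia would be hidden. The protocol does not support either reading. Sections 10.1.2 and 14.5.3.2 compare haemoglobin evolution from D0 to D28 between arms for each episode. Transition tables and per-attack changes from baseline separate pre-dose from post-dose values for every parameter, and the general rules in section 14.5 could supply a test for them. Section 14.5.4.1 tabulates treatment-emergent laboratory events, and section 11.8 flags neutrophils below 400/mm³ and marked ALT rises. But section 11.7 admits laboratory findings as adverse events only when medically relevant, mean changes do not replace graded counts, and simple tests on pooled attacks ignore clustering by child.
- **D0 is not expressly counted.** This stands: section 14.5.4.2 fails to exclude D0 values but does not say that they count, and the sentence can also be read as a comparison over time. The SAP, not shown, may settle this. Still, section 14.1 makes this text the basis of the SAP, and the adverse event rule just before it does contain the missing restriction.
- **A cumulative count has its own meaning.** Children ever abnormal under an assigned regimen is a randomised comparison, whereas a rate over repeat attacks conditions on later events. This supports keeping the count as a summary, not as the test of tolerability.
- **The sizes are assumed.** D0 prevalences and attack means have no source in the protocol, and with equal attack numbers there is no inflation. Balanced D0 abnormality dilutes; it does not bias between arms.

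**Conclusion.** The point holds in limited form. The two-year patient count lacks a condition of new or worsened post-dose grade, lacks scaling to treated attacks, and conflicts with section 10.2.3 on the unit. The contradiction in unit needs no numerical assumption.

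The other two consequences are conditional. Dilution occurs if D0 values are counted: power of about 92-93% falls to 30%, 17% and 10% at assumed D0 prevalences of 30%, 50% and 70%. Excess rejection occurs only if attack numbers differ by arm: about 15-30% at an assumed 8 v 10 attacks, and 5% if they are equal.

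A reader might go further and conclude that the comparison tests malaria burden instead of drug tolerability. That is too strong, because post-dose abnormalities are counted as well; the comparison mixes the two. With haemoglobin and medically relevant events partly covered elsewhere, the gap is mainly the absence of a clustered between-arm comparison of new or worsened grades for ALT, bilirubin, creatinine, neutrophils, leukocytes and platelets. This is a secondary safety analysis, and the primary endpoint is unaffected. The change should be made but is not critical.

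**What to change.** In section 14.5.4.2:

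1. Define a treatment-emergent laboratory abnormality as a post-dose grade higher than that attack's own D0 grade. State which days count, because D14 and D42 are conditional on an earlier abnormal result for most parameters.
2. Compare the arms on it at the first attack, as the randomised comparison.
3. Compare the arms over repeat attacks as a proportion per treated attack, with the child as cluster (GEE or robust variance).
4. Show D0 abnormalities separately by arm as baseline. At a repeat attack soon after the last one, D0 may still carry an effect of the earlier course, which is a further reason to display it.
5. Keep the two-year count of children ever abnormal, if wanted, as a descriptive cumulative summary.
6. Reconcile the unit of analysis between sections 10.2.3 and 14.5.4.2.

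The cost is a wording change and one derived variable; all data are already collected. The counts of abnormal patients will be smaller than under an unrestricted count.

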**During the total follow up of the cohort**

To compare the two groups of treatment in terms of:

- Treatment incidence density
- Impact of repeated treatment on clinical and biological tolerability
- Impact on anaemia
- Impact on Hackett score

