# Patient safety

## Safety instructions

Safety and tolerability of the treatments will be evaluated by recording Adverse Events (AEs) and grading laboratory and vital signs evaluations. A severity grading scale, based on toxicity grading scales developed by the WHO and the National Institutes of Health, Division of Microbiology and Infectious Diseases, will be used to grade severity of all symptoms, physical exam findings, and haemoglobin results (see Appendix 2 and 3).

All laboratories abnormalities on D28 (ref: Appendix 3)

- Grade 2 or more for biological data
- Clinically significant abnormality (whatever the grade)

have to be followed until resolution or progression has to be stabilized.

For each malaria episode, follow-up for safety will be conducted during the scheduled malaria follow-up visits, and at any unscheduled visit. Follow-up for adverse events reported during a given malaria episode will continue until the patient is re-treated with study medications, or the study ends. If an AE is on going at the time of inclusion for a new malaria episode this AE will be recorded as a concomitant disease at D0 (the AE number recorded at the episode where this AE occurred will be specified to link them). At each episode a new cycle of adverse event assessment and reporting will begin according to the definitions of AE and SAE. Each AE will be considered as one until it has recovered.

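### The analysis named for the repeated-treatment tolerability objective pools episodes, with no attack rank, first-attack reference or allowance for several episodes per child, so sub-threshold build-up outside haemoglobin is only described

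*Protocol*

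**What the plan says.** Protocol section 6.2 lists, among the between-arm comparisons over the whole follow-up, "Impact of repeated treatment on clinical and biological tolerability". Section 10.2.3 has the same title and gives the method: adverse events are catalogued by frequency, severity and relationship, the arms are compared with the treated malaria episode as the unit, and the biological parameters are handled in the same way.

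For laboratory data, section 14.5.4.2 says "Absolute and relative changes to the baseline will be computed for each parameter for each attack" and "The evolution between D0 and D7 and D0 and D28 will be analyzed for each attack". Section 14.3.1 defines baseline: "The evaluations used as baseline values will be the last evaluations performed before treatment administration".

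For adverse events, section 11.1 says "Follow-up for adverse events reported during a given malaria episode will continue until the patient is re-treated with study medications, or the study ends". It continues: "If an AE is on going at the time of inclusion for a new malaria episode this AE will be recorded as a concomitant disease", with the safeguard that "the AE number recorded at the episode where this AE occurred will be specified to link them". Section 14.5.4.1 defines treatment-emergent events attack by attack, as events that appear or worsen between the first dose and D42.

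A model with attack rank, arm and their interaction does exist in the protocol, in section 14.5.3.2. It is specified only for success or failure of the treatment response.

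**The concern.** The objective asks what repeated courses do to tolerability. A comparison of arms pooled over episodes answers a different question: whether an average episode on one drug is tolerated worse than an average episode on the other. If each course left a small deficit that had not recovered by the next attack, that deficit would become part of the next D0. Each within-attack change would look the same and the accumulated change would not be estimated.

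There is a second problem with the unit of analysis. The default tests in section 14.5 (Student t or Wilcoxon, chi-square or Fisher) assume independent observations. Episodes from one child are not independent, and children with frequent attacks weigh most. If within-child results are positively correlated, pooled tests on episodes give standard errors that are too small.

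What is at stake is a stated secondary objective. Section 11.8 makes neutropenia and raised ALT events of special interest, and these are among the parameters with no planned analysis across attacks apart from grade counts and raw summaries. The primary analysis is not affected.

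**Working it through.** The protocol gives no figure to reproduce here. The check sets the planned safety analyses side by side and then illustrates the effect of a restarting baseline.

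**Which planned analyses could show change across attacks?**

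| Planned analysis | Section | Across attacks? |
|---|---|---|
| Arms compared by episode | 10.2.3 | No rank, no first-attack reference, no child term |
| Laboratory change, D0–D7 and D0–D28 | 14.5.4.2 | Within each attack |
| Transition tables D0, D7, D28 | 14.5.4.2 | Paired between visit days; no reference to attack 1 |
| Treatment-emergent events | 14.5.4.1 | Defined per attack |
| Raw values at each measurement time | 14.5.4.2 | Can show levels, but unpaired |
| Patients with abnormal values by grade over 2 years | 14.5.4.2 | Yes, once a grade limit is crossed |
| Evolution of abnormal baseline values | 14.3.2.2 | Yes, for values already abnormal |
| Mean haemoglobin, including D0, by episode | 14.3.2.2, 14.5.3.2 | Yes, haemoglobin only |
| Anaemia at D0 of each episode | 10.1.2 | Yes, haemoglobin only |
| Rank, arm and interaction model | 14.5.3.2 | Yes, efficacy response only |

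For non-haemoglobin parameters below the grade limits, only the raw summaries remain. They are unpaired, and only children with many attacks contribute at high ranks, so a change in who contributes can hide or imitate drift.

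**Illustration.** Assume a fraction f of the value is lost at each course and not recovered by the next D0. The protocol gives no such figure, so a range is shown. The within-attack change is -f at every attack; the change from the D0 of attack 1 after k courses is (1 - f)^k - 1. Neutrophils start at an assumed 4000/mm3. Grade 1 in Appendix 3 starts at 1200/mm3.

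| f | Each attack shows | After 3 courses | After 6 | After 10 |
|---|---|---|---|---|
| 5% | -5% | -14.3% (3429) | -26.5% (2940) | -40.1% (2395) |
| 10% | -10% | -27.1% (2916) | -46.9% (2126) | -65.1% (1395) |
| 20% | -20% | -48.8% (2048) | -73.8% (1049) | -89.3% (429) |

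Worked entry: 0.90^6 = 0.531; 0.531 - 1 = -46.9%; 4000 × 0.90^6 = 2126. Only 1049 and 429 reach a grade. The other seven entries do not enter the grade comparison, although the fall from the first D0 is as large as 65.1%.

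**Age and grades.** In Appendix 3 a haemoglobin of 9.5 g/dL is grade 1 below 2 years and grade 2 above; 10.5 g/dL is ungraded below 2 years and grade 1 above. Children enter at 6 to 59 months and are followed for up to 2 years, so a grade can change with no change in the value.

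**The case against.** The strongest reply is that much of the signal is kept. Raw values, grade counts over two years, abnormal baseline values, haemoglobin by episode and anaemia at D0 do not depend on re-baselining. A reader might infer that cumulative toxicity is removed from the analysis altogether; the documents do not support that. For haemoglobin in particular, the evolution across episodes is planned.

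The adverse-event rule is also largely defensible. A carried-over event was counted in the attack where it arose, stays linked by its number, and counts again if it worsens (11.4, 14.5.4.1). Recounting an unchanged event would conflict with section 11.1, which treats it as one event until recovery. What is missing is only a table showing how long such events persist through later courses.

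The illustration is hypothetical: start value, loss and absence of recovery are assumed, and a steady fall would show in the raw D0 means. The transition tables also use laboratory normal ranges, which the protocol does not give, so some values could be flagged abnormal before grade 1.

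The baseline wording in 14.3.1 could be read as the first attack for some purposes. The D0–D7 and D0–D28 contrasts, however, are explicitly per attack.

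On age, randomised arms age alike, so the overall arm contrast needs no age term. That stands, but it does not cover change with attack rank within an arm, or arms compared at the same rank if attack frequency differs.

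Finally, model detail commonly belongs in the statistical analysis plan, which is not shown and may add some of this. But section 10.2.3 is not silent: it fixes a unit of analysis and a comparison, and as written these do not match the objective.

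**Conclusion.** The point holds in limited form. As written, the analysis assigned to the repeated-treatment objective compares arms per episode, ignores attack rank and the pre-first-course value, and does not allow for repeated episodes of one child. Build-up in neutrophils, ALT and the other non-haemoglobin parameters that stays below the grade limits would be seen only in unpaired raw summaries.

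The size cannot be derived from the protocol. Under an assumed unrecovered loss of 5% to 20% per course, the change from the first D0 after six courses is -26.5% to -73.8%, against -5% to -20% in each attack's own table; any recovery between attacks shrinks the gap. This weakens a secondary safety objective and is worth correcting. It is not a claim that such toxicity exists, or that the plan would miss all of it.

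**What to change.** Keep every planned table and add to sections 10.2.3 and 14.5.4.2:

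- For each key laboratory parameter, the within-child change of each later attack's D0 and D28 from the D0 of attack 1, by arm and attack rank.
- A repeated-measures model with child as random effect and terms for arm, attack rank, their interaction and age at sampling, in the form already used for response in section 14.5.3.2, with a similar model for adverse-event incidence per episode.
- A separate table of adverse events carried over as concomitant disease, built from the adverse-event number link in section 11.1, without recounting them as new treatment-emergent events.

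The cost is some extra tables and models; the values, dates and links are already collected. Two limits should be stated in the plan. Attack rank arises after randomisation and reflects attack frequency, itself a compared outcome, so rank-specific arm contrasts are supportive only. The D0 of attack 1 is taken during acute malaria and is not a healthy reference, so D0-to-D0 comparisons are the closest to like-for-like, and D28 changes from it mix drug effect with recovery from disease.
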